### Assessment of Efficacy

The primary efficacy endpoint is a decrease 90 days grade B or C postoperative PF as defined by the last ISGPF classification between patients who receive perioperative somatostatin and octreotide. The definitions of the grade B or C postoperative PF to be used in this study are provided previously. Clinical examination is performed every day to collect manifestations related to PF and its complications. Clinical examination includes temperature, sign of sepsis or infection, and drainage output. Biological evaluation, i.e., amylase dose at 6:00 a.m. on the 24 h drain fluid and blood, is performed on postoperative days 1, 3, 5, and 7 to collect manifestations related to PF. Imaging requested by the clinical manifestation is recorded. Need for reoperation, radiological drainage, and readmission are recorded. Assessment for pancreatic and non-pancreatic complications is made at the time of discharge and in follow-up by the attending surgeon. Pancreatic complications are defined as PF, leak, and abscess. These three complications are typically grouped together because their definitions overlap, the mechanism by which they occur is presumed to be similar (leakage of pancreatic exocrine secretion and/or enteric contents), the presentation is similar (elevated drain output if drain in place or fever/elevated white blood count if no drain in place), and the treatment is the same (percutaneous or operative drainage). When a pancreatic complication has been identified, study drug (somatostatin) or control treatment (octreotide) will be continued until postoperative day 7 and then discontinued. Management of PF is left at each attending surgeon's discretion.

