### Experimental Plan

This is a French comparative multicentric phase III randomized controlled open trial comparing two groups receiving either somatostatin vs. octreotide of patients undergoing PD or DP with or without splenectomy. The study is controlled against octreotide, the gold-standard treatment for the prevention of postoperative PF. The research methodology is deliberately based on the SOM230 previous publication in the NEJM14, to be able to compare the different results [(13) #1171]. In the experimental regimen group, all patients will receive continuous intravenous infusion of somatostatin-14, 6 mg per day during 6.5 days starting just after skin incision and surgical exploration. In the conventional therapeutic strategy group, all patients will receive conventional prophylaxis arm: subcutaneous octreotide 100 μg 3 times a day for 6.5 days starting just after skin incision and surgical exploration (Figure 2). Amylase will be dosed on postoperative days 1, 3, 5, and 7, in the morning on the 24 h drain fluid and blood. Dosage of α-amylase is obtained with enzymatic colorimetric test, coloration intensity being proportional to the α-amylase activity. It is determined by measure of absorbance increase.

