### Sample Size Considerations

In daily surgical practice, pancreaticoduodenectomy represents about 80% of pancreatic resection. According to the last two randomized controlled studies performed in France within the FRENCH network, we can estimate the overall rate of grade B/C pancreatic fistula to be about 30% (Table 4). We hypothesize that the use of somatostatin can decrease this rate to 20%. To detect this difference, with an alpha risk of 5% and a power of 80%, a sample size of 294 eligible patients per arm is necessary. Assuming that approximately between 10 and 20% of the patients will not be resected for clinical reasons, a total of 654 patients should be included. These 654 patients will constitute the primary analysis population.

**Table 4 T4:** Reported rate of pancreatic fistula in recent French studies.

		**Type of surgery**	***n***	**% fistula**	
				**A/B/C**	**B/C**
Pessaux et al. (4)	Randomized controlled trial	Pancreaticoduodenectomy	158	34.2	30.3
Sa Cunha et al. (5)	Randomized controlled trial	Distal pancreatectomy	270	55.6	27.3

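### In this open trial the treating surgeon assesses pancreatic complications, and no arm-masked grading of the grade B/C primary endpoint is described; a modest one-sided grading shift would inflate the chance of a false claim for somatostatin

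*Protocol article*

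**What the plan says.** **Masking.** Experimental Plan: "This is a French comparative multicentric phase III randomized controlled open trial comparing two groups receiving either somatostatin vs. octreotide". One arm has a continuous intravenous infusion and the other has subcutaneous injections three times a day, so the allocation is visible at the bedside.

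**Endpoint.** Assessment of Efficacy: "The primary efficacy endpoint is a decrease 90 days grade B or C postoperative PF as defined by the last ISGPF classification". Statistical Analysis treats it as a binary outcome in a two-sided 5% χ² test.

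**Who assesses.** Assessment of Efficacy: "Assessment for pancreatic and non-pancreatic complications is made at the time of discharge and in follow-up by the attending surgeon". The next sentence of that section counts fistula, leak and abscess as pancreatic complications.

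**Who treats.** Same section: "Management of PF is left at each attending surgeon's discretion".

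**What is recorded.** Same section: temperature and signs of sepsis, drain output, and drain and blood amylase on postoperative days 1, 3, 5 and 7. In addition, "Imaging requested by the clinical manifestation is recorded" and "Need for reoperation, radiological drainage, and readmission are recorded".

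**What access is restricted.** Under Randomization, only the randomization list is kept confidential. That protects allocation concealment. It does not mask outcome assessment.

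**The concern.** A grade B/C endpoint turns on a cut between clinically relevant fistula and lesser leakage. If the person who places a patient on one side of that cut knows the arm, borderline cases can be placed differently by arm. The article says that the definitions of fistula, leak and abscess overlap, and its Discussion states the expectation that somatostatin will lower the fistula rate.

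Such an error is systematic. It shifts the observed difference itself, so more patients make a false rejection more likely, not less. At stake is the only primary endpoint of a phase III superiority trial, with a design difference of 10 percentage points.

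The article's Table 4 suggests how many fistulas lie below the cut. In the cited distal pancreatectomy trial 27.3% had B/C out of 55.6% with any grade, so 1 − 27.3/55.6 = 51% of fistulas were below it. In the cited pancreaticoduodenectomy trial the share was 1 − 30.3/34.2 = 11%. The room for regrading therefore differs by procedure, and the article puts pancreaticoduodenectomy at about 80% of resections.

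**Working it through.** **1. Inputs.** Sample Size Considerations: "we can estimate the overall rate of grade B/C pancreatic fistula to be about 30"%; 20% expected with somatostatin; alpha 5%; power 80%; 294 eligible patients per arm; 654 in total, named as the primary analysis population. Statistical Analysis: two-sided 0.05, χ² test. Randomization: 1:1, so 654/2 = 327 per arm.

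**2. The plan's own figure.** With the pooled-variance formula and no continuity correction,

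n = [1.960·√(2·0.25·0.75) + 0.842·√(0.30·0.70 + 0.20·0.80)]² / 0.10² = 293.2, rounded up to 294 per arm.

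Power at 294 is 80.1%. The total follows from 588/(1 − 0.10) = 653.3, rounded up to 654. Both figures reproduce.

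**3. Effect of differential grading.** Assume no true effect, 30% graded B/C with octreotide, and (30 − s)% with somatostatin because s points are down-graded in that arm only. **The shifts s = 2, 3 and 5 and their direction are assumptions.** With p₁ = 0.30, p₂ = 0.30 − s/100 and p̄ their mean:

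- SE₀ = √(2·p̄(1 − p̄)/n)
- SE₁ = √((p₁(1 − p₁) + p₂(1 − p₂))/n)
- P(significant in favour of somatostatin) = Φ[(p₁ − p₂ − 1.960·SE₀)/SE₁]

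Example, s = 3 and n = 294: SE₀ = 0.03723, so the critical difference is 1.960 × 0.03723 = 0.07297; SE₁ = 0.03721; Φ[(0.03 − 0.07297)/0.03721] = Φ(−1.155) = 12.4%.

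| Shift s | Share of B/C cases (s/30) | Patients of 294 | False claim for somatostatin, 294 per arm | Same, 327 per arm |
|---|---|---|---|---|
| 0 | 0% | 0 | 2.5% | 2.5% |
| 2 points | 6.7% | 5.9 | 7.7% | 8.1% |
| 3 points | 10% | 8.8 | 12.4% | 13.3% |
| 5 points | 16.7% | 14.7 | 27.3% | 29.8% |

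Exact binomial enumeration agrees within 0.2 percentage points. Counting rejections in either direction, the 294-per-arm series is 5.0%, 8.3%, 12.7% and 27.4%. The one-direction series is the relevant one here because the claim in question is superiority of somatostatin.

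**4. When would bias alone probably decide the trial?** With 88/294 on octreotide, the first significant count on somatostatin is 67/294 (z = 1.97; 68/294 gives z = 1.87). That is a difference of 21 patients, or 7.1 points. A false claim becomes about as likely as not at a shift near 7 points.

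**The case against.** **The article does not say who assigns the ISGPF grade.** The sentence naming the attending surgeon covers complications in general, and the trio of fistula, leak and abscess is also the wording of the 60-day secondary endpoint. The full protocol or SAP may provide central derivation or adjudication. This stands in part: a reader might infer that the surgeon's grade is the documented source of the primary endpoint, and the article does not state that. It does state an unmasked assessment of fistula by the treating surgeon, so the point rests on a described procedure and not only on missing detail.

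**The size and direction are hypothetical.** This stands. No misgrading rate is given, and the article calls octreotide the gold standard, so assessors need not lean towards somatostatin. Five points would mean regrading one in six B/C fistulas in one arm only. A reader might infer that the trial is likely to yield a false positive. The documents do not support that: at 2 or 3 points, 92% or 88% of null trials with 294 per arm would still make no claim for somatostatin.

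**A programmed rule cannot classify everyone.** This also stands. Scheduled amylase ends on day 7 while the endpoint runs to day 90. The article allows for patients without a drain. Imaging is recorded only when clinically requested. The ISGPF criteria are in a figure not shown, so it cannot be checked that the recorded items suffice. A reader might take an algorithm as a complete replacement for clinical grading; it is not.

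**Unblinded decisions remain.** Imaging, drainage and reoperation pass through the treating team. The more the grade follows those events, the less room there is for pure regrading, and regrading is all that a masked derivation addresses. This too is correct.

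**Conclusion.** The point holds as a design weakness that should be corrected. In an open trial the article has the surgeon who manages fistula, and who can know the arm, also assess pancreatic complications including fistula. It describes no arm-masked grading of B/C.

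The probabilities in the table show how sensitive the primary test is to a one-sided shift; they do not estimate a bias that has been shown to exist. They assume no true effect, a 30% rate in both arms and down-grading confined to the somatostatin arm. A bias in the other direction would instead work against somatostatin and could hide a real benefit.

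**What to change.** Before database closure, when the article says the SAP will be finalized, prespecify:

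1. A fixed ISGPF derivation of grade B/C from the components already recorded: drain amylase, drain output, signs of sepsis, imaging, radiological drainage, reoperation and readmission. Run it on a dataset without the arm code.
2. One rule, identical in both arms, for cases the derivation cannot classify (no drain, or onset after day 7). Using the surgeon's recorded grade for these is one option.
3. The same primary analysis by surgeon's grade, reported alongside, with a list of discordant cases.

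If the full protocol already has a masked grading step, the SAP should refer to it.

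**Cost.** Programming and SAP text. Treatment, visits and sample size do not change, and no additional assessor is needed. **Downside.** Some cases will still rest on the surgeon's grade, and unblinded imaging and intervention decisions still feed the derivation. Grading bias is reduced; treatment-decision bias is not removed.

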### Sample Size Considerations

In daily surgical practice, pancreaticoduodenectomy represents about 80% of pancreatic resection. According to the last two randomized controlled studies performed in France within the FRENCH network, we can estimate the overall rate of grade B/C pancreatic fistula to be about 30% (Table 4). We hypothesize that the use of somatostatin can decrease this rate to 20%. To detect this difference, with an alpha risk of 5% and a power of 80%, a sample size of 294 eligible patients per arm is necessary. Assuming that approximately between 10 and 20% of the patients will not be resected for clinical reasons, a total of 654 patients should be included. These 654 patients will constitute the primary analysis population.

**Table 4 T4:** Reported rate of pancreatic fistula in recent French studies.

		**Type of surgery**	***n***	**% fistula**	
				**A/B/C**	**B/C**
Pessaux et al. (4)	Randomized controlled trial	Pancreaticoduodenectomy	158	34.2	30.3
Sa Cunha et al. (5)	Randomized controlled trial	Distal pancreatectomy	270	55.6	27.3

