### Randomization

Patients are 1:1 randomized in two groups, in the operating room just after skin incision and surgical exploration to exclude patients with carcinomatosis and metastasis, using permutated blocks of random size to stratify group assignment according to the type of procedure (PD or DP) and the presence or absence of main pancreatic duct dilatation (defined as main-duct diameter of >4 mm at the site of pancreatic transection on preoperative imaging). The randomization list is established centrally by the statistician of the URC et CIC Paris Descartes Necker Cochin before the start of the trial. The document describing the randomization specifications and the randomization list are kept confidentially in a secured place URC et CIC Paris Descartes Necker Cochin. The randomization list is implemented in a randomization tool of the e-CRF on Cleanweb software by the URC et CIC Paris Descartes Necker Cochin. Only the statistician and the person implementing the list in the e-CRF have access to the list during the trial. Randomization is performed by the site staff using the centralized tool in the e-CRF just after skin incision and surgical exploration to exclude patients with carcinomatosis and metastasis.

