### Statistical Analysis

All statistical analysis will be performed with the software at URC et CIC Paris Descartes Necker-Cochin. A Statistical Analysis Plan (SAP) will be written and finalized before study closure, i.e., database closure. The SAP will provide full details of the analyses and data displays.

Descriptive statistics will be presented for each treatment with mean, median, SD, standard error, quartiles, minimum, maximum, and the two-sided 95% confidence limits of mean and median. Frequency tables will be presented where applicable. All statistical tests will be two-sided with an alpha level set to 0.05 and will be adjusted on the stratification variables used for randomization.

The main analysis of the primary efficacy endpoint will be performed on the intention-to-treat population. The superiority analysis will be performed by a χ^2^ test (or by a Fisher's exact test if any expected number was <5) considering the percentage of patients presenting 90-day = grade B or C postoperative pancreatic fistula as defined by the ISGPF. It will be planned to adjust the analysis on the stratification variables (i.e., the type of procedure and the presence or absence of main pancreatic duct dilatation) using a multivariate logistic regression.

The secondary analyses will be performed on the intention-to-treat and per-protocol populations. The 60-day grade 3 pancreatic complication rate (fistula, leak, and abscess), the 90-day overall pancreatic fistula rate (grades A, B, and C), the 90-day overall complication rate (grades 1–5) as well as the severe complication rate (grades 3–5), mortality (grade 5), and readmission rate will be compared between patients who receive perioperative somatostatin and octreotide by χ^2^ tests (or Fisher's exact tests if any expected number was <5).

Secondly, these analyses will be adjusted on the type of procedure and the presence or absence of main pancreatic duct dilatation using multivariate logistic regressions. The overall duration of drainage required in patients who develop pancreatic complications and the overall length of stay will be compared between patients who receive perioperative somatostatin and octeotride using Student's *t* tests (or Wilcoxon rank tests if non-normally distributed).

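### The total of 654 allows for 10% non-resection, not the stated 10–20%, so the 80% power holds at best at the lower end of that range

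*Protocol article*

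**What the plan says.** Sample Size Considerations takes a grade B/C fistula rate of about 30% on octreotide and hypothesises 20% on somatostatin. It concludes that "with an alpha risk of 5% and a power of 80%, a sample size of 294 eligible patients per arm is necessary".

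It then inflates for patients whose pancreas is not removed: "Assuming that approximately between 10 and 20% of the patients will not be resected for clinical reasons, a total of 654 patients should be included". The following sentence reads: "These 654 patients will constitute the primary analysis population". The Statistical Analysis section makes the main analysis of the primary endpoint intention-to-treat, by a χ² test.

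Two other places bear on who the 654 are. The Experimental Plan has patients included, with consent, on the day before surgery. The Randomization section allocates them in the operating room after exploration, so that those with carcinomatosis or metastasis can be left out.

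**The concern.** A range of 10 to 20% and a single total stand in one sentence, and the total follows from the favourable end only. The article gives no reason for choosing that end and no power for the rest of the range. Because 294 is the smallest number per arm that reaches 80%, there is no margin to absorb further losses.

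What is at stake is the stated power. A non-significant result would be read as coming from a trial with a 20% type II error, when the plan's own assumption allows 25% or somewhat more.

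The inflation is also hard to square with the sentence after it. Dividing 588 by 0.90 treats non-resected patients as lost to the analysis, whereas naming all 654 as the primary analysis population keeps them in. The two treatments give different power.

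**Working it through.** **Inputs.** Rates of 30% and 20%, 80% power, 294 per arm, the 10–20% range and the total of 654 come from Sample Size Considerations. The test is two-sided at 5% (Statistical Analysis: "All statistical tests will be two-sided with an alpha level set to 0.05"). Allocation is equal (Randomization: "Patients are 1:1 randomized in two groups").

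**Step 1: the plan's n per arm.** Pooled-variance formula without continuity correction, mean rate 0.25:

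n = [1.960 × √(2 × 0.25 × 0.75) + 0.842 × √(0.30 × 0.70 + 0.20 × 0.80)]² / 0.10² = 293.2, rounded up to **294**. This matches the plan. Power at 294 per arm is 80.1%.

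**Step 2: the plan's total.** 2 × 294 = 588, and 588/0.90 = 653.3, rounded up to **654**. This also matches. The implied allowance is 1 − 588/654 = 10.1%.

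**Step 3: the total over the rest of the range.**
- 15%: 588/0.85 = 691.8, so 692 (38 more than 654).
- 20%: 588/0.80 = 735 (81 more than 654; 736 for equal arms).
- Even the cruder multiplication at 20%, 588 × 1.20, gives 706.

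**Step 4: power with 654.** For rates p₁ and p₂, mean p̄ and m per arm:

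power = Φ{[(p₁ − p₂)√m − 1.960 × √(2p̄(1 − p̄))] / √(p₁(1 − p₁) + p₂(1 − p₂))}

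*Reading A: non-resected patients are not analysed.* Rates stay at 30% and 20%, and m = 654(1 − f)/2, where f is the non-resected fraction.

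*Reading B: all 654 are analysed, and non-resected patients count as fistula-free.* m = 327, and both rates are multiplied by (1 − f). The scoring is an assumption. It is a natural one, because the Abstract defines a fistula as failure of the anastomosis or of the remnant closure, and a patient without resection has neither.

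| Not resected | Resected among 654 | Power, reading A | Rates, reading B | Power, reading B |
|---|---|---|---|---|
| 10% | 589 | 80.2% | 27% vs 18% | 78.8% |
| 15% | 556 | 77.9% | 25.5% vs 17% | 75.8% |
| 20% | 523 | 75.4% | 24% vs 16% | 72.6% |

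**Check.** Exact enumeration of the uncorrected χ² test gives 75.4% to 75.6% at 261 to 262 per arm (A, 20%), and 79.0% and 72.7% for reading B at 10% and 20%. The approximation is adequate.

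**Boundary case.** If all 654 analysed patients are resected, 327 per arm at 30% versus 20% gives 84.1%.

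**The case against.** The strongest objection is that 654 may be the number randomised. Randomisation follows exploration, so some non-resections are removed beforehand. If all of them were, 654 analysed patients would give 84.1% power and there would be no shortfall. This stands as a possibility, and it is why the population has to be named. It is not what the section says, however. The total was reached by adding 10% to 588 for non-resection, an addition with no purpose if the 654 are all resected. The stated aim of exploration is to leave out carcinomatosis and metastasis, which need not cover every clinical reason for not resecting.

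A second objection is that the intention-to-treat rule means nobody is lost. That does not restore the power: under reading B the retained patients add no events, and the shortfall grows.

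Third, the sentence says approximately, and other rounded inputs matter as much. With 294 per arm, a somatostatin rate of 20.5% instead of 20% already gives 75.7%. This bears on severity. It does not make the range and the total agree, since the midpoint of 15% already misses by 38 patients.

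A reader might go further and infer that the trial's power is 75%, or that it must recruit 735. The documents support neither. The 10–20% is a planning assumption, the 75.4% belongs to its upper end with non-resected patients left out, and the article does not settle which patients are analysed.

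**Conclusion.** The inconsistency is real and moderate. The figures of 294 and 654 are each reproducible, but 654 covers only the lower end of the non-resection range given in the same sentence. If the 10–20% applies to the 654, as that sentence reads, the stated 80% holds at best at 10%. The shortfall is about 2 points at 15% and 5 points at 20% if non-resected patients are excluded. It is about 1, 4 and 7 points at 10%, 15% and 20% if they are analysed as fistula-free.

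These sizes rest on the plan's own event rates and, for the second set, on the assumed scoring. The type I error is not affected.

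**What to change.** Reconcile three statements in Sample Size Considerations: the 10–20% range, the total of 654, and the sentence that makes all 654 the primary analysis population.

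1. State whether 654 counts patients included before surgery or patients randomised after exploration.
2. State whether non-resected patients are in the primary analysis and, if so, how the endpoint is scored for them.
3. Restate power across 10–20% for that population:
   - Non-resected patients not analysed: 80.2%, 77.9% and 75.4% at 10%, 15% and 20%. The sentence calling all 654 the primary analysis population then has to change.
   - All 654 analysed, non-resected patients scored as fistula-free: 78.8%, 75.8% and 72.6%.
   - 654 randomised and all resected: 84.1%. The non-resection allowance then belongs on top of 654, in the number to be included.

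Alternatively, justify 10% as the planning value and remove the upper end of the range. Steps 1 and 2 are still needed, because under the second case even 10% gives less than 80%.

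The cost is two or three sentences and, in the first two cases, a slightly less favourable stated power over most or all of the range. No extra enrolment and no change of endpoint or test is asked for.

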**Figure 2 F2:**
[figure not shown]
Experimental plan of PreFiPS study.

Patients with newly diagnosed pancreatic disease undergoing pancreatic surgery are screened for inclusion at the first surgical consultation. All patients fulfilling the inclusion criteria are asked to participate in the study. They are included in the study and sign the informed consent the day before surgery. Patients are 1:1 randomized in two arms, in the operating room just after skin incision and surgical exploration to exclude patients with carcinomatosis and metastasis. Surgical procedure is done according to each attending surgeon's preferences. Patients are seen in clinics 1 month after discharge and at 90 postoperative days. Table 3 resumes the chronology of the research.

**Table 3 T3:** Summary the chronology of the research.

**Actions**	**Inclusion visit**	**Surgery**	**Treatment**	**Postoperative days**	**Follow-up visit**	**End of research**
	**(D-1 month)**	**(D)**	**(during 6.5 days after surgery)(^a^)**	**1, 3, 5, 7**	**(D45 ± 7 days)**	**(D90 ± 10 days)**
Informed consent	(A day before surgery)					
History	X					
Clinical examination	X			X	X	X
Para-clinical examination	X				X	X
Amylase dosage in drain				X		
Tests (biochemistry, hematology, etc.)	X			X	X	X
Randomization		X				
Dispensation of treatment			X			
Compliance				X		
Adverse events				X	X	X
Postoperative quality recovery scale only in patients undergoing pancreaticoduodenectomy	(A day before surgery)			Only POD^b^7		

a *Glycemic controls will be done during treatment. Glycemic controls are routine care in patients candidate for pancreatic surgery*.

b *POD, postoperative day*.

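### The 654 patients called the primary analysis population are a pre-surgery inclusion count; they cannot also be the intention-to-treat set, and 80% power holds only at the low end of the stated non-resection range

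*Protocol article*

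**What the plan says.** Sample Size Considerations takes a grade B/C fistula rate of about 30% under octreotide and 20% under somatostatin and concludes: "with an alpha risk of 5% and a power of 80%, a sample size of 294 eligible patients per arm is necessary". It expects 10–20% of patients not to be resected, asks for 654 to be included, and adds: "These 654 patients will constitute the primary analysis population".

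Three other places bear on this sentence.

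- Experimental Plan (text below Figure 2), on inclusion: "They are included in the study and sign the informed consent the day before surgery".
- Randomization, on allocation: "Randomization is performed by the site staff using the centralized tool in the e-CRF just after skin incision and surgical exploration". The stated purpose is to keep out patients found to have carcinomatosis or metastasis.
- Statistical Analysis: "The main analysis of the primary efficacy endpoint will be performed on the intention-to-treat population".

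The Abstract defines fistula as failure of the anastomosis or of the closure of the pancreatic remnant. The planning rates come from the two trials in Table 4, one of pancreaticoduodenectomy and one of distal pancreatectomy.

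**The concern.** Three sets of patients are in play: included, randomized and resected. The sample size paragraph treats them as one. The step up to 654 exists because some patients will not be resected, yet the next sentence puts those patients back into the analysis population. Patients who leave at exploration, before allocation, have no arm and cannot enter a comparison between arms. Patients who are randomized but not resected cannot have the endpoint as the Abstract defines it.

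At stake is the denominator of the primary percentage. The article gives two descriptions of it that do not agree, and the power statement belongs to a third set, the resected patients. The trial is open, so the denominator should not be left to be chosen once data exist.

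**Working it through.** **Inputs.** Rates of 30% and 20%, 80% power, 294 eligible patients per arm, 10–20% not resected and 654 included are from Sample Size Considerations. The test is two-sided ("All statistical tests will be two-sided with an alpha level set to 0.05"). Allocation is 1:1 (Randomization).

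**Step 1: reproduce 294.** With pooled variance and no continuity correction,

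n = [z(0.975)·√(2·p̄(1−p̄)) + z(0.80)·√(p1(1−p1) + p2(1−p2))]² / (p1−p2)²

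With p1 = 0.30, p2 = 0.20 and p̄ = 0.25: [1.960·√0.375 + 0.842·√0.37]² / 0.01 = 293.1, rounded up to 294. This matches the article.

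**Step 2: reproduce 654.** 2 × 294 = 588, and 588/0.90 = 653.3, rounded up to 654. This also matches. The inflation is therefore for 10% non-resection. At 15% it would be 588/0.85, or 692; at 20% it would be 588/0.80 = 735.

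**Step 3: non-resected patients leave before randomization.** The number randomized is 654 × 0.90 = 589 at 10%, or 654 × 0.80 = 523 at 20%. The intention-to-treat set is then 523–589, not 654.

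**Step 4: non-resected patients are randomized and kept.** Two assumptions are needed that the article does not state: a non-resected patient counts as no fistula, and the non-resected fraction d is the same in both arms. The rates become 0.30(1−d) and 0.20(1−d), with 654/2 = 327 per arm. Power is

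Φ{ [(p1−p2)·√n − 1.960·√(2·p̄(1−p̄))] / √(p1(1−p1) + p2(1−p2)) }

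The table sets this beside the analysis of resected patients only, with 327(1−d) per arm at 30% versus 20%.

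| Not resected | Rates if all 654 analysed | Power, all 654 | Resected per arm | Power, resected only | Lost to dilution |
|---|---|---|---|---|---|
| 10% | 27.0% vs 18.0% | 78.8% | 294 | 80.2% | 1.3 points |
| 15% | 25.5% vs 17.0% | 75.8% | 278 | 77.9% | 2.0 points |
| 20% | 24.0% vs 16.0% | 72.6% | 262 | 75.4% | 2.8 points |

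The last column is taken from unrounded values, for example 80.15 − 78.83 = 1.32 and 75.36 − 72.59 = 2.77.

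**Step 5: split the shortfall at 20%.** The total is 80 − 72.6 = 7.4 points. Of these, 80 − 75.4 = 4.6 points arise because 654 covers only 10% non-resection. The remaining 2.8 points are dilution.

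**Step 6: a mixed case.** If half of the non-resected patients leave before randomization and half after, dilution costs about 0.7 points at 10% and 1.6 points at 20%.

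**The case against.** The operative rule is in Statistical Analysis: the main analysis is by intention to treat. On that view the sentence about 654 is loose wording in a sample size paragraph. Randomization follows exploration precisely so that many unresectable patients are never allocated, and detailed rules for the rest may stand in an SAP that is not shown. Much of this is fair. The missing counting rule alone would be no finding in a condensed article. What stands against the plan is that the article positively names a population that its own sizing and its own sequence of inclusion and randomization rule out.

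A reader might infer that the sentence costs the trial more than seven points of power through dilution. The documents do not support that. The article does not say how the 10–20% divide before and after randomization, and a patient who is never allocated cannot also dilute the comparison. Even if every non-resected patient were randomized, dilution accounts for at most about 2.8 points. Nor does the article say that non-resected patients would count as successes.

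A reader might also infer that the primary set ought to be the randomized and resected patients. That is debatable here. The trial is open and allocation precedes completion of the resection, so leaving resection could be decided with the arm known. Keeping all randomized patients is a legitimate choice for a superiority test and agrees with the stated intention-to-treat principle.

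**Conclusion.** The sentence is wrong as written. Its 654 is a count of patients included before surgery, inflated for those who will not be resected, and it cannot at the same time be the intention-to-treat population. This holds whether the non-resected patients are lost before or after randomization: in the first case the analysis set is smaller than 654, and in the second the 30% and 20% rates no longer describe it.

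The effect on power is moderate and comes mainly from elsewhere. The stated 80% holds only at the low end of the article's own range. It falls to about 75% at 20% non-resection among resected patients, and to about 73% if all non-resected patients are randomized and counted as non-events. These figures assume the planned 30% and 20% among resected patients and equal non-resection in the two arms.

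**What to change.** - Replace the sentence with: '654 is the number of patients included; the primary analysis population is all randomized patients, analysed in the arm assigned.'
- State how randomized but non-resected patients are counted for the primary endpoint, and report an analysis of randomized and resected patients as a sensitivity analysis.
- Have the e-CRF require confirmation that resection is going ahead before it releases the allocation. Allocation already follows exploration, so this only adds a check at that point. It makes the randomized and resected sets nearly coincide and removes most of the possible dilution.
- Restate power as about 75–80% across 10–20% non-resection. If the confirmation step is not adopted and all non-resected patients may be randomized, the matching range is about 73–79%.

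The cost is a less favourable stated power and one extra e-CRF item; the rest is wording. If the sponsor wants 80% across the whole stated range on the resected basis, Step 2 gives 735 included, which is 735 − 654 = 81 more patients. The correction of the analysis population does not depend on that choice.
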